## Abstract

**Background:**

Employment protects and fosters health. Occupational health services, particularly in Finland, have a central role in protecting employee health and preventing work ability problems. However, primary care within occupational health services is currently underused in informing preventive activities. This study was designed to assess whether the recording of work ability problems and improvement of follow-up of work-related primary care visits can reduce sickness absences and work disability pensions after 1 year.

**Methods/design:**

A pragmatic trial will be conducted using patient electronic registers and registers of the central pensions agency in Finland. Twenty-two occupational health centres will be randomised to intervention and control groups. Intervention units will receive training to improve recording of work ability illnesses in the primary care setting and improved follow-up procedures. The intervention impact will be assessed through examining rates of sickness absence across intervention and control clinics as well as before and after the intervention.

**Discussion:**

The trial will develop knowledge of the intervention potential of primary care for preventing work disability pensions and sickness absence. The use of routine patient registers and pensions registers to assess the outcomes of a randomised controlled trial will bring forward trial methodology, particularly when using register-based data. If successful, the intervention will improve the quality of occupational health care primary care and contribute to reducing work disability.

**Trial registration:**

ISRCTN Registry reference number ISRCTN45728263. Registered on 18 April 2016.

**Electronic supplementary material:**

The online version of this article (doi:10.1186/s13063-017-2076-3) contains supplementary material, which is available to authorized users.

## Background

There is a strong relationship between employment and health. Full-time employment protects and fosters health [1–3]. The beneficial effects of work on perceived health status and quality of life can be seen even after re-employment after a period of unemployment [4]. Because of the importance of work for both individual well-being and health, along with national productivity, it is important to ensure that individuals are healthy, maintain their work ability and are able to participate in the workforce. Maintaining work ability, however, is not a simple process. There are several identified risk factors for work disability, including work characteristics [5, 6]; unstable jobs and unemployment [7]; a number of chronic diseases [8]; sickness absence rates [9]; and some personal characteristics, such as socioeconomic characteristics [6], education level [10], gender [11] and age [10]. Most of these risk factors for work disability are related to workplace characteristics [12], and employers can influence these factors by leadership, organisational changes and working arrangements [13]. For effective action, the employer needs collaboration with occupational health services (OHS) that can provide information regarding the early signs of work disability. Collaboration with OHS can continue from early signs of work disability to managing ongoing work disability, such as by modifying work tasks or supporting return to work [14].

Work ability is a central issue in Finland because 7.5% of the working population retire early on disability pensions, which also lowers the average retirement age [5] and productivity. In Finland, OHS monitor and maintain employee work ability and through various activities to prevent work disability and other work-related health problems [15]. The wide mandate of OHS is possible because all employees are required to have preventive OHS by law, and approximately 80% of the working population also receive primary care services through OHS. Investments in OHS have resulted in benefits for organisations and their employees, such as reduction in sick leave [16] and increased profitability [16, 17]. In recent years, disability pension rates have also declined [18]. In Finland, OHS are an important provider of health care, parallel to the private and public sectors [15]. OHS are at a key position of fostering employees’ work ability because they see employees during both preventive and curative activities.

Though progress has been made in reducing work disability, more work is needed in this area, and OHS potential in this respect is underused. There is insufficient information about the extent, impact and actions taken, based on assessments of work ability or diagnoses’ work-relatedness during these visits. Over half of the causes of these visits are work-related (27% caused by work and 52% impair work ability) [19], but this information is rarely used in preventive activities because electronic records do not allow for precise collection and use of this information. Intervening in working conditions from the primary care setting could contribute to improving employee work ability and reducing disability [20].

The trial described in this article is a multi-centre, pragmatic, parallel-group, cluster randomised controlled trial using electronic health records and pension registries to improve the recording of work-relatedness and impact on work ability of primary care visits and ultimately the follow-up of these cases at OHS units in Finland. We follow the standardised Standard Protocol Items: Recommendations for Interventional Trials (SPIRIT) checklist in this report (Additional file 1).

### Aim 1

Our first aim in the present study is to assess the effect of an intervention for improving recording and follow-up of patient primary care visits in occupational health care on medium-length sickness absence. Our hypothesis is that improved recording of work-relatedness and/or effects on work ability during primary care visits and closer follow-up and initiation of actions involving the patient and employer at the workplace will reduce medium-length (4–9 days) sickness absences.

### Aim 2

Our second aim in the present study is to assess the effect of an intervention to improve the recording and follow-up of primary care visits to OHS on work disability pensions as recorded in the central pensions register and long-term sickness absence (9–60 days) as recorded in electronic patient registers. We will also investigate the impact of the intervention on short-term (1–3 days) sickness absences. Our hypothesis is that closer patient follow-up will enable the occupational health (OH) and employer teams to address work ability problems earlier and thus reduce sickness absences and disability pension rates.

### Research question

Does an intervention to improve recording and follow-up of primary care visits’ work-relatedness and their impact on work ability reduce medium-length sickness absences (4–9 days) more than no intervention when measured after 1 year?

## Methods/design

### Trial design

The trial is a multi-centre, parallel-group, pragmatic superiority, cluster randomised controlled trial of 1 year in duration. Each OH unit represents one cluster. Because the intervention is provided to doctors responsible for multiple patients and multiple employer organisations, a cluster design was chosen to decrease contamination bias. The study design was developed in accordance with the SPIRIT guidelines checklist.

### Setting

The study was developed together with Pihlajalinna Työterveys, an OHS provider that is part of a private consortium. At the time of trial initiation, the provider has 22 OH units in different cities and towns across Finland, which together had approximately 67,000 employees on their client lists at the end of 2015. In Finland, approximately 91% of all employees are within the remit of OHS [21], approximately 86% of whom have company-provided primary care services, with the rest receiving legislative preventive services.

### Participants and recruitment

Each OH unit within Pihlajalinna Työterveys had between 500 and 9000 employees on their register. In the study, each cluster is considered an independent unit. All OH units in the consortium with full-time OH staff were selected for the study. Two centres within the same town as a larger centre with part-time OH staff were left out of the study. The intervention training was considered routine staff training. Employees on the register of the OHS in 2015–2017 between the ages of 18 and 65 years will be included in the analysis. The cohort will be open, and employees are eligible if they join the OH register at any time during the study period. An employee visiting any of the 22 OH units were considered eligible for analysis.

### Randomisation and allocation

To allocate OH units into intervention and control groups, a randomisation process using dynamic allocation (specifically minimisation) was used. This method was first presented by Taves [22] and later by Pocock and Simon [23]. The use of minimisation has increased in recent years [24], and it has been suggested as the ‘platinum standard’ of trials [25] because it allows for balance between treatment and control arms. In this trial, we considered the following as potential confounders and included them in the minimisation: (1) the client volume of the OHS separated into three enterprises—small, medium and large, (2) the main sector of the OHS clients (industry vs others) and (3) whether one of the OHS unit’s enterprise clients was a major paper factory or not (the paper factory had instituted large-scale OH interventions in recent years).

We began the randomisation with simple randomisation conducted by the team statistician (NT). We allocated the first four units through simple randomisation (1:1) using the random number generator in the R program (R Foundation for Statistical Computing, Vienna, Austria). For the remaining 18 units, we used minimisation to allocate each OHS unit to either the treatment group or the control group to minimise the total imbalance for potential confounders, continuing with a 1:1 ratio. Because the intervention was embedded in routine practice, allocation was concealed from participants but not from providers or investigators. The concern of lack of blinding during the minimisation process did not apply in this case, owing to the cluster-based design and the fact that both the intervention and control clusters are part of Pihlajalinna Työterveys.

### Assessment points

Baseline information will be assessed for 1 year preceding the intervention, from 1 May 2015 to 1 May 2016. Approximately 72,000 spells of sickness absence were registered among 25,000 clients at Pihlajalinna Työterveys in 2015. For the primary outcome (mean sickness absence of medium length after the intervention compared with baseline), assessment will be conducted by NT after 1 year of the intervention, using data up to 1 May 2017 (*see* Fig. 1 for trial flow and Fig. 2 for SPIRIT diagram). For mean disability pensions per centre, the time will be increased to 31 December 2017, with subsequent analysis hoped for after more funding is received.

**Fig. 1 Fig1:**
[figure not shown]
Trial flow diagram. *OHS* Occupation health services

**Fig. 2 Fig2:**
[figure not shown]
SPIRIT figure: Summarizes the allocation, interventions, and outcomes of the study

### Intervention

All units were informed of the ongoing research and its aims before the start of training. In the intervention group, all doctors and nurses or other OH professionals who are part of intervention units took part in training provided by Pihlajalinna Työterveys. The intervention training started on 1 May 2016. The training lasted approximately 1 h. During the training, the principle of the intervention was explained, and all participants received written instructions on the recording procedure and intervention processes. When physicians or nurses were absent, a follow-up visit or phone call was made to impart the intervention information. Each physician and nurse responsible for a company’s OHS took responsibility for their companies’ employees’ follow-up. The implementation of the intervention was followed by the Pihlajalinna Työterveys trainer, who followed up with nurses and physicians and invited them to personal discussions on the process as necessary.

Figure 3 details the intervention and participant flow. The intervention was designed to first estimate the relationship of the main or additional diagnosis or the visit reason to work. During each primary care visit, the attending physician would assess firstly whether the diagnosis was related to work. Secondly, the client’s risk of applying for a work disability pension was estimated according to four categories: (1) no risk of work disability pension, (2) less than 50% chance of work disability pension in the near future (2–5 years), (3) more than 50% chance of work disability pension in the near future (2–5 years) and (4) immediate risk of work disability pension. This assessment is entered in Pihlajalinna Työterveys’s electronic patient register. Once weekly, all patients are recalled on the electronic system for whom a record of work-relatedness was made. Each case is then assigned to the OH nurse responsible for the patient’s employer relations. The responsible OH nurse then initiates follow-up visits as appropriate. These can include worksite visits; tripartite negotiations between the OH physician, employee and employer; occupational physiotherapy for the employee; occupational psychologists’ assessments; or different kinds of rehabilitation processes at an individual level. When a client is deemed as at greater than 50% risk of work disability, a separate rehabilitation plan will be completed with the client present. This plan will include details on the client’s health status, planned actions for rehabilitation, and follow-up by the OH professionals.

**Fig. 3 Fig3:**
[figure not shown]
Participant flow diagram

The control group did not receive additional training on recording work-relatedness. It is possible that Control group physicians might hear of the intervention and might pay more attention to assessing potential threats to work ability during the intervention. However, no central information is provided regarding the intervention in the consortium, and no formalised information is provided to control units, which may reduce confounding. After the end of the intervention, control units will be given a chance to participate in training and implement the intervention if the results of the intervention were positive. Compliance is checked via regular contacts by the intervention trainer with the OH units, enquiring about implementation and challenges.

### Outcome measures

#### Primary outcome

The primary outcome is reduction from baseline of the mean number of medium term (4–9 days) sickness absences from the workplace per intervention and control centre after 1 year of follow-up as measured by OHS patient records. We chose medium-length sickness absences as the primary outcome to ensure that we have a sufficient number of cases to assess impact. Within the Pihlajalinna Työterveys cohort in 2015, there were 17,794 instances of sickness absences between 4 and 9 days in duration. This outcome is also supported by a large Finnish study on over 6000 municipal workers [26] which indicated that sickness absences of between 4 and 9 days were more prevalent (85.7 and 59.0 per 100 person-years for women and men, respectively) than those over 2 weeks (10+ days) in duration. The study also indicated that self-certified (1–3 days) absences were the most common (156.4 and 96.1 per 100 person-years for women and men, respectively), but these are not reliably available from the electronic patient register held by Pihlajalinna Työterveys. Longer sickness absences (between 2 weeks and 60 days) are less prevalent and had rates of 22.8 and 18.0 per 100 person-years for women and men, respectively, with long absences of over 60 days being relatively infrequent (4.7 and 4.4 per 100 person-years for women and men, respectively) [26]. Shorter (1–3 days) sickness absences were not included as a primary outcome, because they are not reliably available from the patient register, and they have been found not to be associated with disability pensions, except through their association with longer-term (3+ days) sickness absences [9]. Long (3+ days) sickness absence spells have been found to be predictive of work disability before the age of 55 [9] and regardless of health status [27].

#### Secondary outcomes

We will assess the following secondary outcomes:Reduction in mean number of short term (1–3 days) sickness absences from the workplace per cluster from baseline after 1 year from the start of the intervention as measured by self-report recorded on OHS records or OHS records of sickness absenceReduction of mean number of any form of work disability pensions as measured by an employee registering as receiving a work disability pension on the central pensions register from baseline to up to 2 years from the intervention as measured by the entry on the central pensions registerReduction of mean number of long-term (9+ days) sickness absences from the workplace per cluster from baseline to 1 year after the intervention as measured by OHS records

### Power calculation

The pre-study power and sample size calculations for our main outcome were based on data collected in 2015 with estimates of the individuals between the ages of 18 and 65 from the 22 OH units (*n* = 24,892). The 22 clusters had an average size of 2300 individuals. We estimated the intra-cluster correlation coefficient to be 0.05. We used the n4means function in the CRTSize package in R [28], which takes into account that the outcome for individuals cannot be assumed to be independent. We used a two-sided alpha of 5% for our primary outcome, the sickness absences of medium (4–9) days, with an SD of 1.5. With 11 clusters randomised to each arm (assuming 2300 individuals per OHS), the study had 91% power to detect at least a 10% difference between individuals in the intervention and control OHS groups. These calculations showed that even with a 20% loss to follow-up or missing data, we would still have 90% power for the primary analysis.

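### The average cluster size of 2300 in the power calculation does not agree with the 24,892 individuals in 22 units that the same section gives as its basis

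*Protocol article*

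**What the plan says.** The Power calculation section names its data source as 2015 figures, described as "estimates of the individuals between the ages of 18 and 65 from the 22 OH units (*n* = 24,892". The next sentence gives the mean unit size: "The 22 clusters had an average size of 2300 individuals". That size is carried into the calculation. With 11 clusters per arm and "assuming 2300 individuals per OHS", the article reports that "the study had 91% power to detect at least a 10% difference between individuals in the intervention and control OHS groups". The other inputs are a two-sided alpha of 5%, an SD of 1.5 and an intra-cluster correlation (ICC) of 0.05. The section adds that 90% power would remain after 20% loss or missing data.

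Other sections give further counts:

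- Setting: the 22 units "together had approximately 67,000 employees on their client lists at the end of 2015".
- Assessment points: about 72,000 absence spells among 25,000 clients in 2015.
- Participants and recruitment: units hold between 500 and 9000 registered employees, and the analysis is to include registered employees aged 18 to 65 in an open cohort.
- Data analysis: everyone registered at a cluster is analysed within that cluster.

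**The concern.** A mean over 22 units is the total divided by 22. The total, the number of units and the mean are all printed in adjacent sentences, and they disagree by a factor of about two. This is not detail that a journal article has left to a fuller document, because no fuller document could make both sentences true.

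The 2300 is an input to the calculation, not only a description. The number of individuals behind a power statement is what the achieved sample and the allowance for loss are later judged against. As written, a reader cannot tell whether the calculation describes about 25,000 people, about 50,600 or some part of the 67,000. Nor can a reader tell whether it counts everyone registered or only people with a recorded absence.

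**Working it through.** **Step 1. Can 2300 be reproduced from a stated count?**

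| Count (section) | Total | Total / 22 |
|---|---|---|
| Individuals aged 18–65 (Power calculation) | 24,892 | 1,131 |
| Clients with a recorded absence, 2015 (Assessment points) | about 25,000 | about 1,136 |
| Employees on client lists, no age limit stated (Setting) | about 67,000 | 3,045 |

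None gives 2300. In the other direction, 22 × 2300 = 50,600, which is 2.03 times 24,892. The one simple division that comes close is 24,892/11 = 2,263, where 11 is the number of units in one arm.

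**Step 2. Reproduce the stated power.** The article gives a 10% difference but no control mean, so the absolute difference has to be back-solved. With m people per unit, k = 11 units per arm and ICC = 0.05:

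- design effect = 1 + (m − 1) × 0.05
- effective n per arm = 11m / design effect

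For m = 2300 the design effect is 115.95, and effective n = 25,300/115.95 = 218.2. With SD 1.5 and the normal approximation, 91% power needs a difference of (1.960 + 1.341) × 1.5 × √(2/218.2) = 0.474. With a t reference on 20 degrees of freedom it needs 0.499.

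**Step 3. Change only the unit size.** The difference is held at the value that gives 91.0% at 2300.

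| m per unit | Meaning | Design effect | Effective n per arm | Power |
|---|---|---|---|---|
| 2300 | as stated | 115.95 | 218.2 | 91.0% |
| 1,840 | 2300 less 20% | 92.95 | 217.8 | 90.9% |
| 1,131 | 24,892/22 | 57.5 | 216.4 | 90.8% |
| 905 | 1,131 less 20% | 46.2 | 215.5 | 90.7% |

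The t calculation gives the same powers to one decimal. At 3,045 per unit effective n is 218.6, so power would be marginally higher than at 2300. Unit size matters so little because effective n per arm cannot exceed 11/0.05 = 220, however many people each unit holds.

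**Step 4. How far does this depend on the ICC?** The article says "We estimated the intra-cluster correlation coefficient to be 0.05". The smaller values below are assumptions for illustration. The difference is reset each time to give 91% at 2300.

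| ICC | Power at 1,131 | Power at 905 |
|---|---|---|
| 0.05 (stated) | 90.8% | 90.7% |
| 0.01 | 89.8% | 89.3% |
| 0.005 | 88.7% | 87.6% |
| 0.001 | 82.1% | 77.8% |

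**The case against.** The strongest reply is that 24,892 may not be the population to be analysed, so that 2300 could be right and 24,892 merely misdescribed. The figure is very close to the 25,000 clients with an absence in 2015, whereas Participants and recruitment and Data analysis point to all registered employees aged 18 to 65. On that basis 2300 per unit would require 50,600 of the roughly 67,000 listed employees (76%) to be in the age range. The article does not give that count, so it neither confirms nor excludes it. This part of the objection stands, and it means the direction of the error is open. It does not remove the contradiction, because the section itself attaches 24,892 to people aged 18 to 65 from all 22 units.

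Two stronger readings are tempting. A reader might infer that the planned sample is overstated twofold. That holds only if 24,892 is the analysis population; against 3,045 per unit, 2300 would be too low. A reader might also infer that the total was divided by the units of one arm instead of all units. The near match with 2,263 makes this possible, but the article does not say how 2300 was obtained.

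It can also be said that the power statement survives. At the stated ICC it does, since both the 91% and the 90% after loss hold to rounding. That limits the weight of the point without making the printed input correct.

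**Conclusion.** The point holds as an inconsistency in a stated sample-size input. The mean unit size of 2300 differs from the 1,131 implied by the section's own total and number of units, and no other stated count yields it. Which figure is wrong, and in which direction, cannot be settled from the article.

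At ICC 0.05, replacing 2300 by 1,131 lowers power by about 0.2 points, and by about 0.3 points once 20% loss is applied. This rests on the stated ICC, on one average size used for every unit, and on a difference back-solved from the claimed 91%. It would be a misreading to conclude that the discrepancy shows the trial to be underpowered.

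Nor does the small change confirm the 91%. The back-solved difference corresponds, at 10%, to a control mean of about 4.7 to 5.0, which the article does not state. Whether that mean is right for this outcome is a separate question.

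**What to change.** 1. State which population the power calculation and the primary analysis use: all registered employees aged 18 to 65, as Participants and recruitment and Data analysis imply, or only those with a recorded absence.
2. Say what each of 24,892, 25,000 and 67,000 counts.
3. Give the chosen population's total and its true mean per unit. This is 1,131 if 24,892 is the base; otherwise it is the registered total aged 18 to 65 divided by 22. The 67,000 should not be used for this until the age restriction has been applied.
4. Rerun the n4means function with that size and restate the power before and after 20% loss, giving the control mean used.

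Settle the population first. Simply replacing 2300 by 1,131 could fix the wrong denominator if 24,892 covers only people with an absence.

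The cost is one count from data already held, one rerun and a few corrected sentences. The number of clusters and the analysis are unaffected by the correction of unit size.

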### Data analysis

Data will be analysed on the intention-to-treat principle. All employees registered at a cluster will be analysed as part of that cluster. We will use both R and IBM SPSS Statistics software (IBM, Armonk, NY, USA) to analyse the data. We will first examine the data using descriptive statistics. Between-group analysis will be conducted using Pearson’s chi-square test or Fisher’s exact test for categorical data and Student’s *t* test or the Mann-Whitney *U* test for continuous variables, depending on normality of a distribution. The normality of the distribution of the variable will be examined with the Kolmogorov-Smirnov test. The intervention effects for primary and secondary outcomes will be analysed using regression analysis, logistic regression will be used for dichotomous outcome variables, and Poisson regression will be used when the outcome variable is a count. In both analyses, we will examine the impact of, and control for, possible confounders. The regression analysis will result in ORs and rate ratios with 95% CIs. The results will be considered significant at *p* < 0.05. For analysing the differences in duration of sickness absences, we will use Kaplan-Meyer survival curves and the log-rank test.

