## Discussion

The wealth of registers, especially in Nordic countries, allows for innovative research to be conducted with minimal need for additional data collection or trouble for the participants. Recent authors have argued that registry trials can have a wealth of benefits, but quality issues need to be taken into account [29]. Our pragmatic trial uses the combination of electronic health records with registries and tests a real-world intervention with a good study design and maximum external validity [30] with little disruption to the physicians implementing the study [31]. The trial is pragmatic in nature, and thus, while yielding results highly transferable to other settings, there are statistical challenges in design. These include, for example, the high variation in cluster size, which may reduce the power. Regardless of this, we expect the cluster and total sample sizes to be sufficient to detect a true difference, and the impact of the cluster size variation can be determined during analysis.

While interesting from a methodological standpoint, the practical impact of quality improvement in occupational health care has implications beyond this trial and this particular consortium. Through assessment of work-relatedness of each visit, primary care visits can be used effectively as a tool for secondary prevention and early intervention. These approaches can be used also in settings where occupational health care is not statutory. Studies have indicated that the recording of work-relatedness of visits is not optimal [32], and approaches such as this built into services could potentially improve reporting. Improved reporting and recognition can also contribute to collaboration between OHS and employers and general practitioners [33]. These issues are important particularly in Europe, where the population is ageing and life expectancy is increasing and where economic development depends on a healthy workforce.

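### The 91% power assumes 22 equal units of 2300; with units of 500 to 9000 it holds only if the analysis weights units about equally, which the analysis section does not secure

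*Protocol article*

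**What the plan says.** Power calculation (protocol article) uses one common size. "The 22 clusters had an average size of 2300 individuals", and the result is reported as "With 11 clusters randomised to each arm (assuming 2300 individuals per OHS), the study had 91% power". The other inputs are a two-sided 5% alpha, "the sickness absences of medium (4–9) days, with an SD of 1.5", and "We estimated the intra-cluster correlation coefficient to be 0.05". A 20% loss of individuals is said to leave 90% power. The target is a 10% difference; the control mean to which the 10% applies is not given.

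Participants and recruitment says: "Each OH unit within Pihlajalinna Työterveys had between 500 and 9000 employees on their register". Setting gives about 67,000 employees over the 22 units.

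Data analysis says "All employees registered at a cluster will be analysed as part of that cluster" and plans logistic regression for dichotomous outcomes and Poisson regression for counts. It names no unit-level summary, random unit effect or weighting. Primary outcome, by contrast, defines the endpoint as a mean number of absences per centre.

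The Discussion refers to "the high variation in cluster size, which may reduce the power. Regardless of this, we expect the cluster and total sample sizes to be sufficient", and leaves the effect of size variation to be determined at analysis.

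**The concern.** With units this large and an intra-cluster correlation of 0.05, almost all the variance of an arm mean lies between units. What matters is how many units effectively contribute, not how many employees. If each unit counts in proportion to its size, a few large units dominate and the effective number falls below 11 per arm. One unit of 9000 would be 9000/25,300 = 36% of an arm at the stated average size, or 9000/33,500 = 27% if the average is 3045.

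The power section makes no allowance for this, and the Discussion acknowledges it without a number. The stated type II error of 9% therefore depends on an analysis choice that the article does not make. The 20% reserve gives no cover: it allows for fewer individuals, which hardly matters here, and not for fewer effective units.

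**Working it through.** **Inputs.** From Power calculation: k = 11 units per arm, m = 2300, ICC = 0.05, SD = 1.5, two-sided alpha 0.05. From Participants and recruitment: sizes 500 to 9000. From Setting: 67,000/22 = 3045 as an alternative mean size.

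**1. The plan's own figure.** Design effect = 1 + (2300 - 1) × 0.05 = 115.95. SE of the difference = 1.5 × √(2 × 115.95/25,300) = 0.1436. The 91% cannot be reproduced directly because the control mean is missing. Solving backwards, 91% needs a difference of 0.474 (normal) or 0.499 (t, 20 df). This difference is held fixed below, only to isolate the effect of unequal size. Normal and t versions agree within about 0.1 point.

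**2. The 20% loss.** With m = 1840 power is 90.9%, consistent with the stated 90% and under 0.1 point below 91%. Common sizes of 1131 (24,892/22) and 3045 give 90.8% and 91.1%, so the average size hardly matters.

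**3. Smallest spread that the stated range allows.** One unit at 500, one at 9000, the other 20 equal:
- Mean 2300: the 20 units are (50,600 - 9500)/20 = 2055 each; CV = 0.65.
- Mean 3045: the 20 units are (67,000 - 9500)/20 = 2875 each; CV = 0.46.

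**4. Size weighting with valid cluster-level standard errors.** Design effect = 1 + ((1 + CV²)m - 1) × ICC. For CV 0.65 and m = 2300 this is about 164.7, so SE = 1.5 × √(2 × 164.7/25,300) = 0.171 and power = Φ(0.474/0.171 - 1.96), about 79%. The exact column uses the actual size weights within each arm, averaged over random 11:11 splits.

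| Mean size | CV | Status of CV | Design-effect formula | Exact weights |
|---|---|---|---|---|
| 2300 | 0.65 | minimum | 79.1% | 82.0% |
| 3045 | 0.46 | minimum | 85.3% | 86.2% |
| 2300 | 0.80 | assumed | 73.3% | not run |
| 2300 | 1.07 | assumed smooth spread, 500 to 9000 | 61.7% | 63.2% |
| 3045 | 0.86 | assumed smooth spread, 500 to 9000 | 70.7% | 71.3% |

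**5. Near-equal weighting.** The variance of one unit's mean is SD² × (ICC + (1 - ICC)/m). The bracket is 0.05 + 0.95/500 = 0.0519 at the smallest unit and 0.05 + 0.95/9000 = 0.0501 at the largest. Inverse-variance weights, the type a random-effect model uses, therefore differ by under 4%, against 18-fold (9000/500) under size weighting. Power with equal or inverse-variance weights is 90.5-91.0% in every configuration tried, including after 20% loss.

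**The case against.** The strongest reply is that size weighting is nowhere specified. The sentence assigning employees to their cluster sets no weights, the article treats each cluster as an independent unit, and the primary and short- and long-term absence outcomes are defined per centre or cluster. An analysis at that level loses less than one point. A journal article may also leave model details to a fuller document. This stands, and it rules out a reading that a reader might infer: that the planned regression is size-weighted and that power has therefore fallen to some figure on the plan's own inputs. The documents do not say so. What remains is that the article prints a power figure whose validity turns on this choice, pairs it with regression that names no unit-level method, and reassures the reader without a number.

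Second, the loss needs a particular combination: size weights together with valid clustered standard errors. If clustering were ignored altogether, the problem would be false-positive error, a different point. This also stands, so the figures above are conditional.

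Third, no CV is reported, and the 500-9000 range describes register counts, which may belong with the mean of 3045 and not 2300. Both means are therefore shown. Only the upper limits follow from the stated range; any specific lower value, such as 62% or 73%, rests on an assumed spread.

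Fourth, allocation used minimisation that included client volume, not purely random splits. At the minimum CV this matters little: over the splits tried, power ran from 81.5% to 82.5% (mean 2300) and from 85.9% to 86.5% (mean 3045).

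Last, the equal-size assumption is stated openly and the Discussion discloses the issue. That makes it an unquantified limitation, not an arithmetic slip.

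**Conclusion.** The point holds in conditional form. The 91% and 90% belong to a design with equal units, which this trial does not have. They remain about right if units are weighted nearly equally. If units are weighted by size, power is at most about 79-82% (mean 2300) or 85-86% (mean 3045), and lower for spreads wider than the minimum.

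This rests on the stated ICC and SD, on valid cluster-level standard errors, and on a difference solved backwards from the 91%. The figures show how much power unequal size can remove; they are not estimates of the trial's actual power. Nor should a reader take them as confirming the 91%. A difference of 0.474 read as 10% implies a control mean of about 4.7, which the article does not state, whereas the 2015 counts give 17,794/24,892 = 0.715 medium-length spells per person. Which mean the 10% refers to is a separate question.

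**What to change.** 1. **Data analysis:** for the primary outcome, specify either a comparison of unit-level rates (one value per unit, equal weights, about 20 df) or a Poisson model with a random unit effect. Either agrees with the per-centre definition under Primary outcome.
2. **Power calculation:** restate power for that estimator using the observed 2015 unit sizes, and report their CV and the control mean. If size weighting is kept, use the design effect 1 + ((1 + CV²)m - 1) × ICC.
3. **Discussion:** replace the deferral to the analysis with the resulting figure.

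The cost is wording and one recalculation from register counts already held; no further units or data are needed. The downside is that near-equal weighting targets the average unit and not the average employee. If the sponsor prefers the average employee and keeps size weighting, the stated power becomes less favourable.
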